#### **4.10. Secondary safety outcome analyses: AEs and SAEs**

SAEs and AEs will be presented overall and split by MedDRA System Order Class (SOC) and Preferred Term (PT). AEs and SAEs will be displayed as n(%)M where M is the number of events experienced for all children experiencing at least one event ( $M > n$ ).

- SAEs: n(%)M
- Antiseptic related SAEs: n(%)M
- Grade 3 or 4 AEs: n(%)M
- Grade 3 or 4 skins scores (appendix I and II of protocol) : n(%)M
- Grade 3 or 4 hypothermia in neonates only (section 4.7.3 of protocol) : n(%)M

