##### **Neonates:**

Safety will be assessed using a modified skin score which assesses the skin condition, and presence of erythema, dryness, and any other sign of skin damage (see [Appendix I](#))(46,47). This will be performed before each application of antiseptic and 30 minutes after application. The skin score will be considered as both an absolute value and graded. Skin score assessments will be performed once every day on all babies to provide unbiased comparisons across randomised groups.

Temperature will be monitored before and 15 minutes post every antiseptic application. For neonates in the once only and control arms temperature will be measured daily. Guidelines for repeating the temperature if it is out of range will be outlined in the clinical MOP.

Hypothermia will be graded as follows:

- Grade 1: 35.5 - 36.0C
- Grade 2: 35.4 - 35.0C
- Grade 3: 34.0 - 34.9C
- Grade 4:  $<34.0C$

Other adverse events will be monitored for daily and reported as described in [Section 5](#).

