##### **4.10.2.2. Secondary outcome measures**

Mothers:

- Maternal toxicity – score and grade (tolerability and safety)
- Bacterial load in neonates exposed to maternal antiseptic, compared to control
- Serious adverse events

Neonates:

- Adapted neonatal skin condition score (safety) (absolute score and grade)
- Temperature (change in absolute temperature and grade (hypothermia))
- Serious adverse events

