Frequency of SAEs will be tabulated by randomised group, and compared using exact logistic models (or time-to-event models if AEs occur in >10% of the trial population overall). SAEs will also be tabulated by grade. Similar analyses will be conducted for the AEs in [Appendix III](#).

A Statistical Analysis Plan will be written and approved by the DMC before the first interim analysis is reviewed by the DMC.

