#### **5.1.2. Adverse events**

Adverse Events include:

- An exacerbation of a pre-existing illness
- An increase in frequency or intensity of a pre-existing episodic event or condition
- A condition (even though it may have been present prior to the start of the trial) detected after trial product administration
- Continuous persistent disease or a symptom present at baseline that worsens following administration of the trial treatment

Assessment of adverse events (AEs) is challenging in neonates since standard adult grading scales do not apply; for example, normal ranges of laboratory parameters vary with age and normal function is difficult to specify. Adverse events will therefore be assessed using an adapted version of the DAIDS

scale for neonates, that has been used in previous neonatal trials by groups such as IMPAACT(48), including studies conducted for regulatory FDA approval ([Appendix III](#)).

Each adverse event will be assessed at each scheduled assessment and graded by the investigator according to the Adapted DAIDS score for neonates, reproduced from the IMPAACT network(48) and maternal adverse event grading, reproduced from the “Common Terminology Criteria for Adverse Events (CTCAE)” ([Appendix III](#)).

Maternal toxicity and neonatal skin reactions and hypothermia will be separately assessed as part of secondary outcomes and graded according to the classification shown in [Appendix I](#), [II](#) and [Section 4.7.3](#).

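### The SAP specifies no count or comparison by arm of grade 1–2 hypothermia (35.0–36.0C), although hypothermia grade is part of the neonatal secondary outcome

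*Protocol*

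**What the plan says.** Protocol 4.10.2.2 lists, for neonates, "Temperature (change in absolute temperature and grade (hypothermia")). SAP 2.2 repeats this outcome without limiting it to particular grades. Protocol 5.1.2 confirms that grading belongs to the outcome: "Maternal toxicity and neonatal skin reactions and hypothermia will be separately assessed as part of secondary outcomes and graded".

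Protocol 4.7.3 gives the scale: "Grade 1: 35.5 - 36.0C", "Grade 2: 35.4 - 35.0C", "Grade 3: 34.0 - 34.9C", and grade 4 below 34.0C.

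The SAP handles temperature in two places:

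- **SAP 4.9** tabulates mean (SD) temperature at baseline, before application and after application, for babies randomised to treatment. It then fits a mixed model to the pre-to-post change. Standard-of-care (SOC) babies are left out of that model, although a later bullet in the same section refers to a comparison with SOC.
- **SAP 4.10** has one graded line for hypothermia: "Grade 3 or 4 hypothermia in neonates only (section 4.7.3 of protocol").

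**The concern.** The outcome has two halves, change and grade. The SAP analyses the first and, for the second, counts only the two most severe grades. No table, count or model is named for grades 1 and 2.

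This matters because the pilot is meant to choose a regimen on safety as well as efficacy. Protocol 6.2.1 names hypothermia after first-day chlorhexidine cleansing as an observed risk and gives safety as a main reason for the trial. Protocol 4.6.2.5 lists a temperature below 36.0C immediately before application among the circumstances for considering interruption. Readings from 35.0C to just under 36.0C meet that trigger, yet nothing in the SAP says how many babies in each arm had them.

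The gap looks like an oversight. For the parallel safety outcome, skin score, SAP 4.8 tabulates every score value at each time point, in addition to the grade 3–4 row in SAP 4.10. Hypothermia has only the grade 3–4 row.

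**Working it through.** The plan states no rate, power or sample size for hypothermia, so there is no figure to reproduce. The check sets the texts side by side and adds two illustrative calculations.

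**1. What is counted** (bands from protocol 4.7.3, outputs from SAP 4.9 and 4.10)

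| Grade | Band | Count specified in SAP |
|---|---|---|
| 1 | 35.5–36.0C | none |
| 2 | 35.0–35.4C | none |
| 3 | 34.0–34.9C | yes, pooled with grade 4 |
| 4 | below 34.0C | yes, pooled with grade 3 |

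Grades 3–4 together are readings below 35.0C. The uncounted band is 35.0–36.0C.

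**2. How much of graded hypothermia lies in the uncounted band.** The documents give no temperature distribution, so this is an assumption with a range. Assume single readings are Normal with mean m (35.8–36.8C) and SD s (0.3–1.0C), recorded to 0.1C. Any grade is then a reading below 36.05, and grade 3–4 a reading below 34.95.

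Share in grades 1–2 = 1 − Φ((34.95 − m)/s) / Φ((36.05 − m)/s)

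| m | s | Any grade | Grade 3–4 | Share in grades 1–2 |
|---|---|---|---|---|
| 36.5 | 0.5 | 0.184 | 0.0010 | 99.5% |
| 36.5 | 0.8 | 0.287 | 0.0263 | 90.8% |
| 36.0 | 1.0 | 0.520 | 0.1469 | 71.8% |
| 35.8 | 1.0 | 0.599 | 0.1977 | 67.0% |

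Over the whole grid the share runs from 67.0% to nearly 100%. It is the larger part in every case examined, but how large depends on the assumed mean and spread.

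**3. Whether the worst grade per baby would be a fair comparison.** Maximum readings per baby, from protocol 4.7.1.2:

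- SOC: baseline plus 24, 48 and 72 hours = 4.
- Single application: pre-application, 15 minutes after, then 24, 48 and 72 hours = 5.
- Multiple application: before and 15 minutes after each of four applications = 8.

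Take an assumed mean of 36.7C and SD 0.5C in every arm, with no treatment effect. The chance that one reading is graded is Φ((36.05 − 36.7)/0.5) = Φ(−1.3) = 0.097. With independent readings, P(at least one graded) = 1 − (1 − 0.097)^k:

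- k = 4: 1 − 0.903^4 = 34%
- k = 5: 1 − 0.903^5 = 40%
- k = 8: 1 − 0.903^8 = 56%

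Correlation between a baby's readings would narrow this gap but would not remove it. A worst-grade comparison would therefore favour SOC over multiple application through measurement frequency alone. SOC babies also have no post-application reading.

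**The case against.** The strongest reply is that cooling is already analysed. SAP 4.9 reports temperature before and after application at all time points and models the change by antiseptic and frequency, which is the temperature analysis that protocol 4.10.4 describes. A general fall after application would show in those means. SAP 4.10 also opens by saying that adverse events will be presented overall and by MedDRA term, which could include hypothermia, and SAP 4.9 allows further analyses.

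Much of this stands. A reader might infer that almost all hypothermia would go unreported, and the documents do not support that. They give no temperature distribution, and grade 1–2 readings still enter the means and, in treated babies, the change model. A reader might also take protocol 4.10.4, "SAEs will also be tabulated by grade", as a promise to tabulate all adverse events by grade. That sentence concerns serious events, and protocol 5.1.2 places hypothermia separately under the secondary outcomes. The point does not rest on it.

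The reply does not supply the grade half of the outcome. Means and a mean change do not say how many babies fell into each grade, and a modest average shift can hide a tail of cooled babies. The adverse-event sentence promises no grades, and the graded adverse-event row beneath it is again "Grade 3 or 4 AEs: n(%)M". The change model leaves out SOC, so it gives no comparison with control. Permission for additional analyses is not a specification.

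**Conclusion.** The point holds as a mismatch between a named secondary outcome and its specified analysis. Hypothermia grade runs from 36.0C down in both documents' outcome definition, but the SAP counts only readings below 35.0C. Grades 1–2 have no specified count or comparison by arm.

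The loss is limited to the graded count. Mean temperature and pre-to-post change are still reported for treated babies, and severe grades are still counted. The share of hypothermia in the uncounted grades is unknown; the range of about 67% to nearly 100% rests wholly on assumed Normal distributions of single readings and should not be quoted as an expected figure. No sample size or power statement in the plan is affected, and no view is taken on which temperature threshold is clinically right. The SAP should be corrected because the outcome is a safety outcome and the correction is nearly free.

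**What to change.** In SAP 4.9 or 4.10, add n (%) for each hypothermia grade (none, 1, 2, 3, 4), with the number of babies measured, by antiseptic, by frequency and for SOC, at matched readings:

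- the 15-minute reading after the first application, for the treated arms;
- the daily pre-swab readings at baseline, 24, 48 and 72 hours, for all arms including SOC.

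Keep the existing grade 3–4 row. If any-grade hypothermia is compared between arms, do so only at these matched time points. Do not compare the worst grade over all readings, for the reason shown in the third step of the working.

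The cost is SAP wording and a few extra table rows. The temperatures are already collected under protocol 4.7.1.2, and no clinical rule changes.

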#### **AE and SAE analysis**

- Frequency of SAEs will be compared using exact logistic models.
- Time-to-event models will be used if AEs/SAEs occur in >10% of the trial population overall.

#### **4.11. Additional secondary efficacy outcomes analysis**

##### **Log CFU of specific species**

- Will be analysed as per the primary outcome.
- Analyses beyond the primary analysis will be performed if considered necessary.

##### **Acquisition and loss of specific species**

- Will be analysed as per the primary outcome except Binomial generalised linear mixed models will be fitted with logit link will be used.
- Analyses beyond the primary analysis will be performed if considered necessary.
- Margins will be taken for presentation of results.

##### **Components of total CFU considered separately**

- Will be analysed as per the primary outcome.
- Analyses beyond the primary analysis will be performed if considered necessary.

##### **Components of skin scores considered separately**

- Will be analysed as per total skin score above.
- Analyses beyond the primary analysis will be performed if considered necessary.

## 6. Appendix: Bayesian priors

### 6.1. Non-informative priors

Non informative priors were selected to capture a wide range of possible values. The same priors will be used for the maternal and the neonatal strata.

- Intercept mean =4, sd = 50
- Difference mean =0, sd = 20

### 6.2. Informative priors (optimistic and sceptical)

Informative priors were determined based on NeoCHG data (unpublished) and expert clinician opinion ([name], [name], [name], [name], [name]) during an online meeting on 21/03/2023. There is a lack of robust data to support the use of strong priors, especially in the maternal strata.

#### Intercept specification

The intercept (Control) was selected as data from NeoCHG could be used. The maternal strata will use data from d8 in NeoCHG, reflecting bacterial load with time to accumulate, whereas the neonatal strata will use data from baseline reflecting the recent birth of the neonates. Using mean values from the study and approximations of sd with a multiplier on the sd to capture extra uncertainty, the intercepts will be specified as following a normal distribution with parameters:

- Log CFU in maternal strata: mean 8.4; standard deviation 2.6; multiplier 3
- Log CFU in neonatal strata: mean 4.5; standard deviation 3; multiplier 2

A higher multiplier was chosen for the maternal strata as there is greater uncertainty in the expected values. Priors may be reformulated to a reference of 1%CHG/once before analysis to match reference specification in focal analysis.

#### Difference specification

Clinicians specified the mean difference that optimistic and sceptical persons knowledgeable on the topic might assume, using a reference of no antiseptic application. The approach taken was that both optimistic and sceptical persons were assumed to have some belief that the opposing view could be correct, given the assumption of equipoise for the trial to be able to go ahead. The mean values selected were:

#### Maternal strata

| Parameter          | Optimistic mean | Sceptical mean |
|--------------------|-----------------|----------------|
| 0.5% CHG           | Lower by 0.5    | No effect      |
| 2% CHG             | Lower by 1      | No effect      |
| OCT                | Lower by 1      | No effect      |
| Single application | Lower by 0.5    | No effect      |

|                      |            |           |
|----------------------|------------|-----------|
| Multiple application | Lower by 1 | No effect |
|----------------------|------------|-----------|

### Neonatal strata

| Parameter                 | Optimistic mean | Sceptical mean |
|---------------------------|-----------------|----------------|
| 0.5% CHG                  | Lower by 0.5    | No effect      |
| 2% CHG                    | Lower by 1      | No effect      |
| Emollient                 | Lower by 1      | No effect      |
| Alternate day application | Lower by 0.5    | No effect      |
| Control                   | Lower by 1      | No effect      |

Larger differences were selected than those found in NeoCHG due to the differing site conditions in NeoVT-AMR.

Differences were specified to follow a Normal distribution with mean as above and a certain percentage of the distribution more extreme than the opposing value (sceptical for optimistic priors and optimistic for sceptical priors) reflecting probability of alternate scenario being correct. This equates to a Normal distribution with:

- Mean = optimistic or sceptical mean
- $sd = \text{abs}(\text{sceptical mean} - \text{optimistic mean}) / \text{critical\_value}$

Where the critical value is from the t-distribution with infinite degrees of freedom and probability equal to the alternate scenario being correct.

The probability of the alternate scenario being correct was

- Maternal strata: 0.2
- Neonatal strata: 0.1

A larger probability was chosen for the maternal strata to reflect the greater uncertainty in the this strata.

Plots of the differences are:

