## 1. Trial design

### 1.1. Design & outline

NeoVT-AMR is a randomised controlled factorial trial with 3x2 + standard of care (SOC) design with two independent strata – labouring mothers and hospitalised neonates. Within each stratum, 147 individuals will be recruited – 21 per treatment combination or SOC. Additionally, 147 babies from mothers in the maternal stratum will also be swabbed at birth.

The two factors are:

- Antiseptic: 1% chlorhexidine (CHG), 2% CHG and octenisept (OCT)
- Frequency of application: once only and multiple applications

Multiple applications timings are 0/4/8/24/28/32h in maternal strata and 0/1/2/3d in neonatal strata.

The SOC group will receive standard of care. For analyses, the reference arm will be 1% CHG once only as there are more effective replicates of each of the factorial arms and therefore greater power for comparison than with SOC. 1% CHG once only was selected as it would be the most straightforward to implement and CHG is more widely available than OCT so evidence of superiority of OCT over CHG would have to be shown for implementation to be advised.

The trial design is summarised in the trial scheme below. Note that the ‘once only’ frequency boxes are (n=21) also.

[figure not shown]

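### The informative-prior tables in SAP 6.2 name arms this trial does not have, and no rule says how the antiseptic and frequency priors combine against standard of care

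*Protocol*

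**What the plan says.** SAP 1.1 defines two factors for both strata: "Antiseptic: 1% chlorhexidine (CHG), 2% CHG and octenisept (OCT") and "Frequency of application: once only and multiple applications". It adds that "Multiple applications timings are 0/4/8/24/28/32h in maternal strata and 0/1/2/3d in neonatal strata".

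Protocol 4.10.4 promises a Bayesian analysis with optimistic, non-informative and sceptical priors. SAP 4.6 (Bayesian analysis) fits the same model as the primary analysis. It reports posterior probabilities for each factor against SOC and between levels within a factor. Its focus is on non-informative priors, with informative priors as a sensitivity analysis unless the non-informative model has fitting problems.

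SAP 6.2 (Difference specification) says the mean differences were elicited "using a reference of no antiseptic application". The tabulated values are:

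| Row | Maternal label | Neonatal label | Optimistic mean | Sceptical mean |
|---|---|---|---|---|
| 1 | 0.5% CHG | 0.5% CHG | -0.5 | 0 |
| 2 | 2% CHG | 2% CHG | -1 | 0 |
| 3 | OCT | Emollient | -1 | 0 |
| 4 | "Single application" | "Alternate day application" | -0.5 | 0 |
| 5 | "Multiple application" | Control | -1 | 0 |

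Each prior SD is the absolute difference between the sceptical and optimistic means divided by a critical value: "Where the critical value is from the t-distribution with infinite degrees of freedom and probability equal to the alternate scenario being correct". That probability is 0.2 for mothers and 0.1 for neonates. SAP 6.2 (Intercept specification) also allows the priors to be re-expressed against 1% CHG once before analysis.

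**The concern.** Two separate problems arise.

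The first is labelling. An analyst working from the SAP alone has no prior for 1% CHG in either stratum. In neonates there is also none for OCT, single application or multiple application. The neonatal table gives Control an effect of -1, although the stated reference is no antiseptic. Since 1% CHG once is the reference to which the priors may be re-expressed, the missing 1% CHG row blocks that step too.

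The second is combination. Every treated participant has one antiseptic level and one frequency level, and both sets of rows are effects against the same untreated reference. The primary model is additive in the two factors. If both sets of rows enter it as coefficients against SOC, the shared effect of being treated at all is counted twice.

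At stake is the pre-specification of the informative-prior analyses. If labels and coding are settled after efficacy data by arm are known, those analyses lose most of their value as a robustness check.

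**Working it through.** **Step 1: levels against rows.** Five levels need a prior: 1% CHG, 2% CHG, OCT, single and multiple.
- Maternal table: four are present. 1% CHG is missing (1 of 5).
- Neonatal table: only 2% CHG is present. 1% CHG, OCT, single and multiple are missing (4 of 5).
- The five neonatal values (-0.5, -1, -1, -0.5, -1) equal the maternal values row for row. This suggests labels carried over from another trial. The opening of SAP section 4 has a similar slip, where it describes the frequency groups as working days and alternate working days.

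**Step 2: reproduce the stated tails.** The formula is sd = |difference| / z(1 - p), read as one-tailed because the SAP speaks of the part of the distribution beyond the opposing value.
- Maternal, p = 0.2, z = 0.8416: sd = 1/0.8416 = 1.188 and 0.5/0.8416 = 0.594.
- Neonatal, p = 0.1, z = 1.2816: sd = 1/1.2816 = 0.780 and 0.5/1.2816 = 0.390.

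For a single optimistic row, P(no benefit) = Φ(-mean/sd) = Φ(-z), which is 0.20 or 0.10 as stated. Row by row, the specification is coherent.

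**Step 3: add the two sets of rows.** Assume that both sets enter as independent additive coefficients against SOC, with the 0.5% CHG row read as the lowest CHG level and the neonatal rows matched to the maternal ones by position. The cell mean is the sum of two rows, and the cell sd is the square root of the summed squares.

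| Cell v SOC | Optimistic mean | sd, maternal | P(no benefit), maternal | sd, neonatal | P(no benefit), neonatal |
|---|---|---|---|---|---|
| Lowest CHG, single | -1.0 | 0.840 | 0.117 | 0.552 | 0.035 |
| Lowest CHG, multiple | -1.5 | 1.328 | 0.129 | 0.872 | 0.043 |
| 2% CHG or OCT, single | -1.5 | 1.328 | 0.129 | 0.872 | 0.043 |
| 2% CHG or OCT, multiple | -2.0 | 1.680 | 0.117 | 1.104 | 0.035 |

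The six-cell average is -(1.0 + 1.5 + 1.5 + 2.0 + 1.5 + 2.0)/6 = -1.58. The antiseptic rows average -(0.5 + 1 + 1)/3 = -0.83 and the frequency rows -(0.5 + 1)/2 = -0.75. The ratios are 1.9 and 2.1.

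**Step 4: what is not doubled.**
- Within-factor contrasts, with the 0.5% row read as 1%: 2% CHG v 1% CHG is -1 - (-0.5) = -0.5, OCT v 1% CHG is -0.5, and multiple v single is -0.5. Each uses one set of rows only.
- Sceptical means stay at 0 + 0 = 0. Only the cell sd grows, by at most √2 = 1.41 relative to the larger of the two rows (1.188 to 1.680 maternal, 0.780 to 1.104 neonatal).

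**Step 5: the text does not settle the SOC contrast.** For 2% CHG with multiple application against SOC, three readings are open:
- a single row's value: -1;
- 1% CHG once v SOC taken as -0.5, plus the two within-factor steps: -0.5 - 0.5 - 0.5 = -1.5;
- the sum of both rows: -1 - 1 = -2.0.

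Coding all five levels against SOC also gives six parameters, including the intercept, but a design of rank 5 over the seven arms. The data alone then cannot separate the two shared effects.

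**The case against.** The strongest reply is that this is a labelling slip in a sensitivity analysis. The neonatal values are all present and match the maternal table, so the intended rows are easy to surmise. The frequentist model is primary, the Bayesian focus is on non-informative priors, and SAP 4.6 says that analyses beyond the primary may not be presented. The optional re-referencing to 1% CHG once would leave within-factor contrasts free of any double count. All of this limits the consequence. It does not remove the problem: the SAP does not authorise matching rows by position, neither table has a 1% CHG row to re-reference to, and SAP 4.6 still plans contrasts with SOC.

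A reader might infer that the plan doubles the elicited effect in both the optimistic and the sceptical analyses and in both strata. The documents do not support that.
- The SAP does not state the additive coding against SOC, and its primary model lists no SOC level.
- Every sceptical mean is zero, and each sceptical SD is set from its own row's undoubled difference.
- No value for a combined cell is recorded as elicited, so -1 for 2% CHG with multiple application is the value in each row, not an elicited figure for the pair.
- Doubling in neonates presupposes that the rows have been relabelled.

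A reader might also infer that the neonatal informative analysis is impossible or that the odd rows should be deleted. Neither follows. The numbers exist, and deletion would discard the values that by position correspond to OCT, single and multiple.

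**Conclusion.** The point holds in two parts, with different certainty.

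The label mismatch is plain on the page: one of five levels lacks a prior in mothers and four of five in neonates, and the neonatal table gives its own reference an effect. The neonatal informative-prior analyses, and re-referencing to 1% CHG once in either stratum, cannot be carried out from the text without guessing.

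The missing combination rule is also real, but its effect is conditional. If both sets of rows were entered additively and independently, optimistic prior means against SOC would be about twice the single-row values on average. For 2% CHG or OCT with multiple application, the prior probability of no benefit would fall from the stated 0.20 to about 0.12 in mothers, and from 0.10 to about 0.035 in neonates (rows matched by position).

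The frequentist primary analysis and the non-informative Bayesian analysis are untouched. The informative priors would carry more weight only if the non-informative fit failed. The correction should be made, but the main results do not depend on it.

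**What to change.** Before efficacy data by arm are seen, revise SAP 6.2 as follows.

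1. Reconcile the row labels in both tables with the levels in SAP 1.1, using the record of the elicitation meeting. Relabel the rows and keep the values. If the record does not show which level a value was given for, ask the same clinicians.
2. State one parameterisation for combining antiseptic and frequency priors against SOC. Six cell-against-SOC priors would serve. So would one any-antiseptic effect plus within-factor differences, but no any-antiseptic prior is recorded as elicited, so that route needs a new elicitation.
3. Tabulate the implied prior mean, SD and tail for each contrast with SOC, and confirm that they agree with the elicited mean and the 0.2 or 0.1 tail.

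The cost is one revised appendix and a check against the elicitation record, plus a short further elicitation if the second parameterisation is chosen. No change to design, data collection or the primary analysis is needed.
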